# Evaluation of a community-based integrated care model (CIE) for frail older people in rural Foshan, China: study protocol for a stepped-wedge cluster randomized controlled trial {1}

**DOI:** 10.1186/s13063-023-07328-7

**Published:** 2023-05-08

**Keywords:** Integrated care, Chronic care model, Community-based eldercare, Community-based rehabilitation, Primary healthcare, Stepped-wedge trial, Frail elderly, Quality of life, Process evaluation

## Abstract

**Background:**

While community-based eldercare has proven to be effective in qualitative studies, there is limited evidence on the effectiveness of this geriatric care model in rural communities where caring for older people is traditionally the responsibility of family members, but a formal long-term care was recently introduced in China. CIE is a rural community-embedded intervention using multidisciplinary team, to provide evidenced-based integrated care services for frail older people including social care services and allied primary healthcare and community-based rehabilitation services.

**Methods:**

CIE is a prospective stepped-wedge cluster randomized trial conducted at 5 community eldercare centers in rural China. The multifaceted CIE intervention, guided by chronic care model and integrated care model, consists of five components: comprehensive geriatric assessment, individualized care planning, community-based rehabilitation, interdisciplinary case management, and care coordination. The intervention is rolled out in a staggered manner in these clusters of centers at an interval of 1 month. The primary outcomes include functional status, quality of life, and social support. Process evaluation will also be conducted. Generalized linear mixed model is employed for binary outcomes.

**Discussion:**

This study is expected to provide important new evidence on clinical effectiveness and implementation process of an integrated care model for frail older people. The CIE model is also unique as the first registered trial implementing a community-based eldercare model using multidisciplinary team to promote individualized social care services integrated with primary healthcare and community-based rehabilitation services for frail older people in rural China, where formal long-term care was recently introduced.

**Trial registration {2a}:**

China Clinical Trials Register (http://www.chictr.org.cn/historyversionpub.aspx?regno=ChiCTR2200060326). May 28th, 2022.

## Introduction {6a}

Reforming eldercare delivery to meet the multiple needs of an increasing number of frail population is a top policy agenda in many countries around the world [1]. The challenges are particularly acute in rural China, where informal care network is weakened due to the out-migration of young working-age adults to urban areas and decreasing birth rate [2]. The issue is further compounded by the fact that government-run institutions and senior care homes in China are reserved for those with no children, no income, and no known relatives [3]. Privately operated facilities are seen as the fastest way to meet the demand. However, the initiatives have apparently not served their intended purpose partly because of its inconsistency with filial piety of traditional Chinese Confucian philosophy and the stigma of nursing homes. Specifically, the current practice of private-for-profit services caused a huge financial burden for older residents and their families, with additional challenges coming from the lack of professionals and paraprofessionals [3]. Provision of community-based care for frail older people through integrating existing human resources with suitable local conditions is a potential strategy to deal with the diverse needs of older people [4]. Under this model, older people do not need to move out of the home and the community provides day care in the form of visiting service or staying in a daycare center [4]. Yet, implementation of such an innovative eldercare model is challenging.

The integration of health services and social services for senior residents has gained tremendous attention in recent years [5]. Evidence suggests that older people will have better health outcomes, enhanced satisfaction and decreased costs if a person-centered coordinated care is provided in the community [6, 7]. Though widely acknowledged and pursued, several gaps in implementing such models exist. First, in China, routine healthcare is practiced through a tiered healthcare delivery system whereby each level of healthcare facility (tertiary, secondary, and primary) would deliver care according to their designated functions [8]. This adds to the list of barriers to prevention and treatment of cases and scale up of services in eldercare institutions because they are financed, governed, and managed separately. Primary healthcare providers are in a central position to coordinate the changing needs of the ageing population in many countries, yet their role of coordinating with specialty care has not reached its full potential in China [9]. Second, many eldercare practice modes only provide several simple medical examinations and treatments, such as health checkup, prescribing drugs, and basic first aid [4]. Such activities may be effective in yielding positive changes in certain groups, but, in the real world, a model with a more person-directed approach to engaging individuals in decision-making is needed. In contrast to the geriatric model, several integrated care approaches at the community setting have been proposed, but they have only targeted a single chronic disease (e.g., stroke), outcomes (e.g., quality of care, costs), or process (communication, team building) [10–12].

Further evidence is also necessary on an integrated care model for frail older adults. An important distinction between chronic disease and frailty is that frailty is more often associated with functional impairments and physical inactivity that require a restorative or enabling approach [13]. This study aims to address this gap. We developed an integrated care model guided by the concepts and practice of community-based rehabilitation (CBR) for frail older people, named Community-based Integrated Eldercare (CIE). Unlike a typical Western model of CBR that is integrated into primary healthcare systems, CBR service in primary healthcare centers of China remains in a low quality due to poor education and systematic training on general practitioners even though these centers have been equipped with the newest equipment and technology [14]. This current CIE intervention includes the elements of a CBR delivered by specialists in physical and rehabilitation medicine (based on a more level model of delivery of rehabilitation services). In addition, CBR is a specific intervention appropriate for the Chinese culture using traditional methods (e.g., moxibustion, traditional Chinese medicine fumigation, massage, cupping therapy and skin scraping) as the practical entry point to promote inclusion and participation of people in the local community. Another unique aspect of this study is the proposed CIE model will be tested at community eldercare centers (CECs) in rural China, a novelty formal long-term care form developed in a few cities, but was recently expanded to the rural population [4].

The objective of this study is to evaluate the effectiveness of a community-based, multidisciplinary, integrated care model for the frail older people named Community-based Integrated Eldercare (CIE). The specific aims are:Evaluate the efficacy of CIE model to improve functionality and dependency, cognitive and emotional status, and quality of life and enable frail older people to live in the community for longer.Process evaluations to gain insights into applying the same model to different settings in the future.

## Methods

### Study design {8}

This study will adopt a multicenter, prospective, unidirectional randomized controlled trial using a stepped-wedge cluster design with repeated cross-sectional samples. Four phases will be sequentially rolled out over 48 weeks: preparation, control phase (standard care exposure), transition phase (intervention introduction), and intervention exposure (Fig. 1).

**Fig. 1 Fig1:**
[figure not shown]
Stepped-wedge study design in 5 community eldercare centers (clusters)

The stepped-wedge design offer advantages in pragmatic community trials when an intervention can only be delivered in a staggered manner to account for practical logistics constraints. Additionally, stepwise implementation allows all participants to receive the intervention at some time during the study which is ethically appropriate [15].

### Study setting {9}

The model is implemented in Lishui county, located in the middle of Pearl River Delta in Southern China. At the end of 2019, the population of Lishui county was 580,000, 22.3% of which are above 60 years of age [16]. The county is divided into 2 blocks with a total of 36 villages. A majority of Lishui’s rural young population have migrated to urban areas for better opportunities and income. As a result, older people is left behind and forced to take care of themselves. In terms of eldercare and healthcare services, Lishui has 18 Community Eldercare Centers (CEC), 1 Primary Healthcare Center (PHC), and 18 Primary Healthcare Stations (PHS) staffed by 130 general practitioners (GPs) and 79 nurses, along with a tertiary comprehensive hospital which provides additional human resources (such as geriatrician and rehabilitation specialist) for geriatric care. Community-based care for older people is primarily delivered by social workers at the CECs and the GPs also visit older people on a 3-monthly basis. The tertiary hospital has in-patient and out-patient services for older adults with multiple health needs, and limited follow-up care following discharge.

### Study sites and participants {10}

Five CECs were purposively selected based on geographic location and representativeness of the frailty in Lishui county.

Study sites were purposively selected in collaboration with villagers committee and Bureau of Civil Affairs according to the following criteria: (1) sites where CBR services were delivered by the tertiary hospital; (2) at least 20,000 visits per year altogether in selected CECs. Based on previous data in the county [17], we assumed each site may be able to see on average 40 frail older people and they are present at least 100 days per year (eight per month); (3) routine eldercare available onsite; (4) no previous introduction of interventions/organizations for integration or increasing services, apart from CIE that is considered as standard-of-care throughout the whole study period.

Study participants consists of all the adults aged 65 or older who are present for care in the selected CECs and agree to participate during the study period. Inclusion criteria are as follows: (1) with household registration in Lishui county; (2) not planning to move away from Lishui county in the prospective follow-up of the study; (3) Chinese version of Mini-Mental State Examination score ≥ 20; (4) written informed consent to participate in the study. For those who had difficulty in writing, informed consent was obtained from their spouses/children. The oral informed consent was recorded when the older people or their family members cannot write. Exclusion criteria are as follows: (1) on a waiting list for a nursing home; (2) with a terminal medical condition; (3) older adults who have psychiatric disorders or other illnesses that require hospitalization; (4) older adults who are currently receiving specialist geriatrician intervention and/or care coordination.

### Intervention: the CIE model {11a}

#### Theoretical rationale

The CIE model is guided by the evidence-based Chronic Care Model (CCM) and the multidisciplinary integrated care model through a restorative or enabling approach specified for the community-based eldercare system in China [18, 19]. Minkman et al. theorized how to implement integrated care and identified two most fundamental principles: engaging and empowering people and communities, population-oriented, and focusing on promoting health [20]. Given the fact that frailty is more often associated with functional impairments and physical inactivity that require a restorative or enabling approach beyond the scope of a traditional CCM [13], we constructed four key components of the CIE model as follows: comprehensive geriatric assessment, individualized care planning, community-based rehabilitation, interdisciplinary case management, and care coordination. The CIE model was originally developed by our research team, which has expertise in chronic disease management and eldercare system in rural China. The model was further refined based on literature and expert review, consultations with representatives from villagers committee, feedback from field staff, and also a pre-test of intervention components. Details of the CIE model are listed in Table 1.

**Table 1 Tab1:** Description of the CIE model: components and implementation information {13}

Components	Outcomes	Providers	Place	Time	Dose
Comprehensive geriatric assessment (CGA)	Profile registration form including medical history, functional scales and service demand evaluation in social work practice	GP-rehabilitation doctor-social worker	At each CEC or at each home	At T0	At least Once Anytime needed (condition change of residents)
Individualized care planning (CP)	A written checklist form	GP-rehabilitation doctor-social worker Residents/family members/caregivers	At each CEC or at each home	Right after the CGA is done at T0	At least Once Anytime needed (condition change of residents)
Community-based rehabilitation (CBR)	Individualized, written plans with goals, timeline, and therapies	Specialists in physical and rehabilitation medicine	At each CEC or at each home	When CGA and CP are done	At least twice a week
Interdisciplinary case management (ICM)	A written checklist form	GP-rehabilitation doctor-social worker Residents/family members/caregivers Facilitated by enablement officer and coordinator team	At each CEC	When a relevant case is found	At least once a month
Care coordination (CC)	Shared information among stakeholders Coordinated action among service providers	The onsite coordinator team facilitated by enablement officer	-	The whole study period	-

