### Outcomes {12}

The outcomes will be measured four times at (1) T0 (2 weeks, the end of preparation period), T1 (6 weeks; the end of observation period), T2 (28 weeks; 20 weeks after the beginning of the intervention), and T3 (48 weeks; the end of the intervention). Outcome data will be collected by external research assistants trained by the CIE research team (Table 1).

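### Table 1 ties CIE components to T0 (week 2) or to the entire study, which as written puts them in usual-care time; they should be tied to each site's crossover

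*Protocol article*

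**What the plan says.** Table 1 lists the five components of the CIE model with a time and a dose for each.

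- **CGA:** at T0.
- **Care planning:** "Right after the CGA is done at T0".
- **CBR:** "When CGA and CP are done", at a dose of "At least twice a week".
- **Interdisciplinary case management (ICM):** triggered by a relevant case, at least monthly, with no link to T0 or to crossover.
- **Care coordination:** "The whole study period".

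Outcomes {12} supplies the only definitions of the time labels: "T0 (2 weeks, the end of preparation period"), "T1 (6 weeks; the end of observation period") and "T2 (28 weeks; 20 weeks after the beginning of the intervention").

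Study design {8} orders the phases after preparation as "control phase (standard care exposure), transition phase (intervention introduction), and intervention exposure". Comparator {6b} gives usual care in the control period and says that CGA and CBR are then not normally multidisciplinary or systematic. The Randomization and blinding section says that all sites begin in usual care, that the sequence is concealed for the first 6 weeks, and that a 2-week transition of training and coordination comes before crossover.

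**The concern.** In a stepped-wedge trial the treatment contrast is the difference between time before and time after each cluster's crossover. The protocol therefore has to be exact about when each component may begin. Table 1 is where the article fixes that timing, and staff at the centres would reasonably look there. It attaches the first two components to a label that marks the start of observation under usual care, makes CBR follow directly from them, and runs care coordination through the entire study. If staff followed it, residents counted as controls would already have been assessed, have a care plan, and be receiving rehabilitation and coordination under CIE. The control condition would then no longer be the usual care that the Comparator section describes.

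**Working it through.** **Inputs.** T0 = week 2, T1 = week 6, and T2 = week 28, which is 20 weeks after the intervention begins (Outcomes {12}). Concealment lasts 6 weeks and transition 2 weeks (Randomization and blinding). Component times come from Table 1.

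**Step 1: reproduce the intervention start.**
- From T2: 28 − 20 = week 8.
- From randomisation: 6 + 2 = week 8.

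The two routes agree, so the protocol's own timeline puts the earliest CIE start at week 8.

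**Step 2: place T0 against it.**
- T0 to T1: 6 − 2 = 4 weeks, all usual care.
- T0 to earliest start: 8 − 2 = 6 weeks, made up of 4 weeks of usual care and 2 weeks of transition.

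**Step 3: set each component beside the phase it falls in.**

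| Component | Time as written | Phase under the other sections |
|---|---|---|
| CGA | T0, week 2 | End of preparation, start of usual-care observation |
| Care planning | Directly after CGA at T0 | Usual care |
| CBR | Once CGA and care planning are complete | Usual care, unless those two are delayed |
| ICM | When a case arises | Not tied to any phase |
| Care coordination | Entire study | Includes weeks 2 to 6 of usual care and the transition |

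Three entries (CGA, care planning, care coordination) conflict with the control phase directly. CBR conflicts through its dependence on the first two. ICM does not conflict, but nothing confines it to time after crossover.

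**Step 4: try the readings that would remove the conflict.**
- *T0 is counted on each site's own clock.* T0 still ends preparation and still comes before T1. If T2 is on the same clock, the start is week 8 of that clock and T0 is again 6 weeks earlier.
- *The CGA at T0 is only baseline measurement.* Table 1 lists CGA as an intervention component given by the GP, rehabilitation doctor and social worker. Outcome data are collected by external research assistants. Care planning and CBR also follow on from this CGA.
- *T0 is redefined elsewhere.* No section of the article does so.

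**The case against.** The best reply is that the rest of the protocol shows what was meant. The Procedure section puts provider training and the setting up of the coordinator team before consent, and consent before CGA. The Randomization section places training in the 2-week transition and links the notice to each site with the start of recruitment there. Read together, these put CGA after a site's step notice. The Procedure and Table 1 both sit under the description of the CIE model, while the comparator has its own section. On this view the fault is a label in a table.

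Much of this stands. Delivery after crossover was probably intended, and the point should not be read as saying that the trial will give CIE to its controls. What does not fall away is the stated rule. The Procedure makes CGA follow consent without mentioning crossover, no text changes the meaning of T0, and the care coordination entry spans the control phase without relying on T0 at all. An intention pieced together from two sections does not replace explicit timings that say otherwise.

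**Conclusion.** Wrong as written. Table 1's timings start CIE components 6 weeks before the earliest permitted start, 4 of those weeks being usual care, and so contradict the control phase set out in three other sections. This rests on the single definition of T0 and on a week-8 start that two routes confirm. Neither the size nor the direction of any bias can be derived, because the documents do not show that the literal timings would be followed.

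Three stronger inferences are tempting, but the documents do not support them.

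- **A count of contaminating CBR sessions.** At two per week, a reader might compute 4 × 2 = 8 before T1 and 6 × 2 = 12 before week 8, and far more at later sites. This assumes that CGA and care planning are finished in week 2, before trained teams exist, and that the same residents are followed although the samples are repeated cross-sections. For later sites it also needs a step schedule that the text leaves unsettled: the Abstract has monthly intervals, while the Randomization section has five sites, the full number, in the first step. Fig. 1 is not shown.
- **A failure of the Hussey and Hughes model to separate contamination from period effects.** That depends on assuming common calendar rounds for all sites. If it held, it would be a question of identifying the treatment effect with or without contamination, and so a separate matter.
- **Site criterion (4) as proof that CIE runs from the outset.** Its wording about CIE as standard care is unclear, but it is an eligibility rule on earlier integration programmes and times no component.

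**What to change.** 1. Keep T0 for outcome measurement only, and give each site's randomised crossover its own label, for example C0.
2. Re-time Table 1: CGA at or after C0; care planning after CGA; CBR when both are done; ICM only after C0; care coordination for residents from C0 to the end of the study.
3. Leave staff training and the setting up of coordination in the 2-week transition, and say so, so that starting resident-level coordination at C0 does not clash with the transition activities in the Randomization section.
4. State in the Procedure that CGA is done only in sites that have crossed over.

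The cost is wording: one new label, four time entries in Table 1 (CGA, care planning, ICM and care coordination, with the CBR entry following from the first two), a note on the transition, and one sentence in the Procedure. No new data, sample or analysis is needed. If delivery after crossover was always intended, the edits only record it.

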#### Components of CIE

Comprehensive geriatric assessment (CGA): It is a multidimensional, multidisciplinary diagnostic process that aims to determine a frail elderly person’s medical, psychosocial, and functional capacities and problems [21]. Unlike traditional geriatric care models, care teams in CIE consist of a general practitioner, a nurse, a rehabilitation doctor, and a social worker. We adopted certain domains identified and recommended by the WHO as needing assessment [21]. Based on these domains, different tools have been embedded in the profiling. Thus, by completing CGA, members in the care team obtain a list of valuable and valid data for each resident. These results work as a decision-support tool to develop an overall care plan and long-term follow-up.*Individualized care planning(CP)*: CP provides a guide for organizing and prioritizing care delivery. Based on information from CGA results, the care team in each CEC develops a care plan for each individual specifically addressing how individual or family preferences are or can be incorporated in care planning processes or the care plan itself. To support CP, the CIE program provides a set of checklist forms that involve actions of each party. Unlike the traditional, provider-driven process of data collection, assessment, and care plan development, the checklists are based on the key principles of a person-directed care planning: autonomy, personhood, and the strengths-based approach, viewing each resident as a unique individual who brings distinct and critical perspectives to care planning [22]. Care teams can also revise the checklists to ensure care plans remain aligned with the needs and preferences of individuals. This practice of integrating the person’s goals in care planning and iteratively revising care plans is rare in eldercare facilities in China.*Community-based rehabilitation(CBR)*: Unlike traditional studies applying CBR that target a single disease, CIE targets frail older people with multiple needs, for which CBR is essential for achieving and maintaining optimal functioning. The key activities of a CBR program comprise of organizing training sessions, providing assistance (health education, assistive devices, and housing adaptation), and extending social and recreational support [23]. CBR is not a new concept, but almost all the eldercare facilities in rural China admitted they did not do CBR at all due to limited resources, or CBR was delivered by volunteers or GPs who have limited systematic training in rehabilitation [23]. In the CIE model, specialists in physical and rehabilitation medicine are responsible for CBR. Guidelines for the CBR were developed based on formal research studies, diverse experiences of disability, best practices drawn from similar approaches, as well as the research team’s own expertise [24].*Interdisciplinary case management (ICM)*: Case management is a collaborative, client-driven process characterized by exchanging ideas and opinions among team members for the provision of quality health and support services [25]. Through ICM, care teams have a shared vision on the content of the care, enabling consensus among stakeholders and reducing duplication of services. For frail older adults, they do not have to repeat their stories to every member of the care team. In the CIE model, a geriatric nurse practitioner is assigned as a case manager who supports the multidisciplinary team by arranging meetings and streamlining the necessary exchange of information. During the meeting, care plan will be approved, actions and care paths will be discussed, and agreements will be made about the care to be deployed and the activities of all persons involved.*Care coordination (CC)*: CC is a key construct for delivering integrated care for community-dwelling residents [26]. The CIE model facilitates communication between service providers and frail older residents in the community using evidence-based reports, reflecting a novel eldercare mode in rural China. The CIE model provides individualistic reports to four involved stakeholders: CECs administrators, contracted eldercare service providers (rehabilitation professionals and social workers, primary health care staff), and frail older residents and their family members/caregivers. Administrators receive a summary report regarding residents profile, care needs, and care plans. Moreover, the report for the elderly and their caregivers is summarized in a relatively simple way. Explicit attention is paid to the necessary support and guidance of the caregivers. The research team and care team also uses WeChat, a free mobile messaging application for communication throughout the program implementation and evaluation.
